## Methods/design

### Design

This study is an unblinded, non-randomized, multi-centre (4 sites), double-arm, controlled trial with 1:1 assignment. The duration of the study is 3 years and includes literature review, development of the app, clinic and patient recruitment, intervention delivery, as well as, data collection and analysis.

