#### Information and education

Comprehensive text and video material aim to educate the patients and provide information on the disease, the artificial joint, the joint replacement procedure and everyday life after surgery. The preoperative phase focuses on information on the physiology of knee or hip, osteoarthritis, as well as, pain and pain management, but also gives a preview of daily activities with an artificial joint and support possibilities.

Patients will be prepared for the hospital stay and surgery by giving information on how to deal with allergies, general preparation for surgery, medication especially on pain and other pain management interventions [27].

The intra- and postoperative phase contains information on the hospital stay and the procedure itself, complications and how to prevent them, wound care, bowel function and body hygiene.

In the rehabilitative phase and home environment, users are encouraged to take part in their pain management, as well as, in their wound and scar care by frequent monitoring with the tools provided in the app. They are given information on rehabilitation, sports, sleep, sexual activity and returning to work post surgery. Users are offered 8 video clips with short and simple exercises to train muscles and increase flexibility in the legs for either knee or hip surgery (e.g. seated leg extension, elevation of legs while sitting) [31].

RECOVER-E proposes a certain number of repetitions and sets per exercise, which gradually increase after hospital discharge and after rehabilitation to keep training motivationally attractive. However, users are requested to first consult their physiotherapist to individually decide on the appropriate exercise intensity at any stage.

Since emotional well-being is closely and positively linked to the experience of control over one’s own recovery process, RECOVER-E provides important information on symptoms and self-management in the immediate postoperative phase. The app also motivates users to ask family and friends for support in order to bridge difficult and frustrating time periods during the first weeks after surgery [32].

Overall RECOVER-E’s education abilities aim to prepare users for an everyday, joint-sensitive life after their joint replacement surgery.

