### Outcomes

Data presented in Table 1 will be measured in the study.

**Table 1 Tab1:** Study measures to be collected

Measure	Instrument	t_0_	t_1_	t_2_	t_3_	t_4_
Primary outcome measure						
Activities of daily living (ADL)	KOOS/HOOS subscale ADL (self-reported)	x				x
Secondary outcome measures						
Pain, symptoms, Sport & Rec and quality of life	KOOS/HOOS subscales pain, symptoms, Sport & Rec and quality of life (self-reported)	x				x
Pain at rest	NRS (self-reported)	x	x	x	x	x
Pain during activity	NRS (self-reported)	x	x	x	x	x
Preoperative anxiety and depression	HADS (self-reported)	x	x			
Other measures						
Usage metrics	number of user sessions, length of time participants interact with the app, content they engage with, frequency of recording self-monitoring parameters, number of awards	continuous recording				
Physical activity	IPAQ (self-reported)	x				
Social support	questionnaire (self-reported)					x
Physician visits post-surgery	questionnaire (self-reported)					x
Use of pain medication	medical record, questionnaire (self-reported)		x	x	x	x
Sex, age	medical record				x	
BMI (size, weight)	medical record				x	
Operated joint	medical record				x	
OPS, ICD	medical record				x	
Comorbidities	medical record				x	
Duration of hospital stay	medical record				x	
Type and duration of planned and performed rehabilitation programme	medical record, questionnaire (self-reported)				x	x
Complications post-surgery	medical record, questionnaire (self-reported)			x	x	x
Structural data of hospitals						
- Number of beds - Number of joint replacement surgeries performed over the past 12 months - Number of nurses in the orthopaedic departments: nurses, nursing assistants, Pain Nurses, full-time equivalent - Number of physicians in the orthopaedic departments: total number, number of orthopaedic specialists, full-time equivalent - Process quality management data for the care of patients with THR/TKR (documentation forms and guidelines, interprofessional standard operating procedures for analgesic therapy, pain management guidelines, other pain therapy guidelines, standard operating procedures for patients with THR/TKR, special contracts with other facilities and mandatory health insurance companies for structured patient care) - Regular cooperation with institutions of inpatient or outpatient rehabilitation						

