### Sample size

Based on the primary outcome ADL subscale of the KOOS/HOOS and the assumable clinical relevant change of 10 points [37, 44, 45], we expect that the group using the mobile app in addition to the standard care will improve at least 10 points more than the control group after having undergone TKR/THR 3 months post-surgery.

To allow for separate analysis of patients with knee and hip OA, 58 knee patients and 58 hip patients are required to detect a difference of 10 points on the HOOS/KOOS ADL subscale (SD 15, power = 0.80 and α = 0.05) [37, 44, 46]. Allowing for 20% dropout [47–49], 5% complications post-surgery [50] and 4% erroneous records, a total of 160 patients will be recruited.

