### Data analysis

Baseline data, clinical and demographic characteristics will be presented to show the baseline comparability of the intervention group and the control group. The analysis will include all patients following the intention-to-treat principle, drop-out and loss to follow-up will be described. Data will be checked for completeness and normality. The treatment effect will be evaluated by the change in ADL using between group analyses, such as independent t-test and ANCOVA to adjust for demographic factors such as age, sex, BMI (body mass index), baseline pain, anxiety, joint, comorbidities, physical activity, pain medication, type and duration of rehabilitation and social support on change in outcomes. For comparison within groups paired t-tests will be conducted. Within the intervention group the relationship between usage metrics and patient reported outcomes will be analysed using linear regression analyses.

All statistical analyses will be performed using IBM SPSS Statistics for Windows, version 24 (IBM Corp., Armonk, N.Y., USA).

Results of the study will be presented at conferences and placed in journals.

The controlled trial will be accompanied by multi-perspective qualitative research approaches to understand user decisions and long-term user engagement of the intervention. These studies will be reported elsewhere.

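### The ANCOVA adjusts for pain medication and social support, which are recorded after app access and which the app sets out to influence, so the adjusted effect may be biased

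*Protocol article*

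**What the plan says.** All references are to the protocol article.

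- **Data analysis.** The treatment effect is evaluated on change in ADL by between-group analyses, with the independent t-test and ANCOVA given as examples. The ANCOVA is to adjust for factors described as demographic. They include age, sex, BMI, baseline pain, anxiety, joint and comorbidities, and then "physical activity, pain medication, type and duration of rehabilitation and social support on change in outcomes".
- **Outcomes, Table 1.** The row "Use of pain medication" is ticked at t1, t2, t3 and t4, not at t0. Social support is ticked at t4 only. Planned and performed rehabilitation is ticked at t3 and t4. IPAQ physical activity is ticked at t0 only, and HADS at t0 and t1.
- **Intervention group.** Participants receive the app link immediately after the t0 assessment, 4–6 weeks before surgery.
- **Information and education.** The app informs on pain medication, and "users are encouraged to take part in their pain management". On support: "The app also motivates users to ask family and friends for support". On rehabilitation, users are given information.
- **Discussion.** Social support is named among the ways in which mHealth is meant to improve health outcomes.
- **Participants and recruitment.** Assignment is by calendar period: January to May 2019 for control, June to October 2019 for the app.

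**The concern.** The study hypothesis concerns the whole effect of using the app on ADL at 3 months. A covariate that the app itself can change does not belong in a model for that effect. If the app improves function partly by getting patients to use analgesics differently or to call on family, holding those variables equal between groups subtracts that part. If the covariate also shares unmeasured causes with ADL, such as how well the patient is recovering, conditioning on it can introduce a new bias whose sign cannot be predicted.

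This matters more here than in a randomised trial. The groups are sequential cohorts, so the adjusted model is the one expected to deal with confounding. As worded, it handles confounding and at the same time conditions on consequences of exposure. A reader could not tell whether a gap between the unadjusted and adjusted results reflects confounding removed or app effect removed.

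**Working it through.** **1. The plan's own figure.** The Sample size section states that "58 knee patients and 58 hip patients are required to detect a difference of 10 points", with "SD 15, power = 0.80 and α = 0.05"; the Design section gives a "double-arm, controlled trial with 1:1 assignment". Sidedness is not stated. The standardised difference is 10/15 = 0.667. A one-sided t-test needs 28.5, so 29 per arm, or 58 per joint, which is the stated figure (power 0.806). A two-sided test would need 37 per arm, or 74, so the stated figure reproduces only one-sided. For losses the plan allows "20% dropout [47–49], 5% complications post-surgery [50] and 4% erroneous records": (58 + 58)/(0.80 × 0.95 × 0.96) = 116/0.7296 = 159.0, which agrees with 160. The 10 points are the full between-group difference, with no allowance for a part removed by adjustment.

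**2. Timing and role of the covariates.**

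| Covariate | Measured | What the article says the app does |
|---|---|---|
| Pain medication | t1–t4 | informs on it; encourages taking part in pain management |
| Social support | t4 only | motivates users to seek it; named as a route to benefit |
| Rehabilitation, planned and performed | t3, t4 | informs about it; not said to change type or duration |
| Physical activity (IPAQ) | t0 only | measured before access; valid covariate |
| Anxiety (HADS) | t0 and t1 | lower preoperative anxiety is a hypothesis; time point for the model not separately stated |

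A late tick is not decisive by itself. Sex, age, BMI, joint and comorbidities are also recorded at t3, yet they describe the patient before app access. Pain medication and social support differ because late recording and a stated app influence coincide.

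**3. If the covariates mediate.** Let m be the share of the total effect that runs through them. The group coefficient after adjustment is 10 × (1 − m). The documents give no m, so the values below are assumptions. Power is one-sided at 29 per arm with SD held at 15.

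| m | Adjusted effect | Simulated mean (116 patients, 2000 runs) | Power |
|---|---|---|---|
| 0 | 10 | 9.96 | 0.81 |
| 10% | 9 | 9.00 | 0.73 |
| 20% | 8 | 7.98 | 0.64 |
| 30% | 7 | 6.98 | 0.54 |
| 50% | 5 | 5.11 | 0.35 |

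The unadjusted estimate stayed at about 10 throughout. The power column is a guide only. Adjusting for prognostic covariates normally lowers the residual SD, so these are not the power values of the planned ANCOVA.

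**4. If they do not mediate but share a cause with ADL.** Suppose the app raises the covariate by 0.5 SD, and an unmeasured factor has correlation c with the covariate and ±0.5 with ADL (SD 15), within group. The covariate's slope is then ±15 × 0.5 × c = ±7.5c, and the adjusted effect is 10 ∓ 7.5c × 0.5 = 10 ∓ 3.75c. For c = 0.3 this gives 8.9 or 11.1; for c = 0.5, 8.1 or 11.9. Simulation gave 8.9 and 11.1, and 8.1 and 11.8. These inputs are assumed too; they show only that the bias can go either way.

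**The case against.** - **The unadjusted t-test is also planned, and no ANCOVA is designated primary.** This is true, so a reader who infers that the total effect is lost from every analysis goes too far. But the t-test does nothing about confounding between calendar periods, and the article itself calls the non-randomised assignment a major limitation. The adjusted estimate still has to be sound.
- **Collection time is not causal time.** This stands in part. Pain medication recorded at admission may reflect earlier use, and the content of the social support questionnaire is not shown. Even so, no t0 value exists for either, so the schedule offers nothing to serve as a baseline covariate.
- **Rehabilitation is not shown to be an app target.** This stands. It is tempting to put it with the other two, but the app is only said to inform about it, and users enter their rehabilitation dates so that content adapts. The planned type may be set by the care pathway and may differ between periods for reasons unrelated to the app, in which case leaving it out could add bias. Performed rehabilitation is nevertheless post-exposure and may itself reflect recovery.
- **Anxiety may mean baseline anxiety.** The word baseline, placed before pain, can be read to cover it. Use of the t1 value, which is a secondary outcome, is a possible inference that the text does not state. Naming t0 would settle it.

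**Conclusion.** The point holds for pain medication and social support. Both have no t0 value, are recorded after app access begins, and are things the app is described as influencing. Adjusting the treatment effect for them can remove any part of the effect that runs through them, or bias it up or down.

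The size is unknown. The 9 to 5 points for 10% to 50% mediation are an illustration on assumed shares, not an estimate. A reader might infer that the ANCOVA necessarily removes part of the effect, or that a third to a half is lost. The documents support neither: attenuation depends on actual mediation, which they do not quantify, and bias through shared causes can also inflate the estimate. For rehabilitation the conclusion is weaker: the performed programme is post-exposure, while the planned programme may be a legitimate confounder.

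**What to change.** Restrict the main adjusted ANCOVA to variables measured at or fixed before app access: baseline ADL, age, sex, BMI, joint, comorbidities, t0 NRS pain, t0 HADS anxiety and t0 IPAQ. State the time point of each. Where a value is taken from the record at t3, specify that it describes pre-access status.

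Remove pain medication and social support from that model. Analyse them as outcomes or in an exploratory mediation analysis.

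Put rehabilitation into a labelled sensitivity model, using the planned type if it can be shown to be fixed by the care pathway.

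The cost is a change of analysis wording, with no extra data or patients. The downside is that differences in rehabilitation between the two periods that have nothing to do with the app are addressed only in the sensitivity analysis, so that result should be reported beside the main one.

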### Ethical considerations

This study is approved by the Ethics Committee of the Medical Association Westphalia-Lippe and of the Faculty of Medicine of the University of Münster (approval number: 2017–329-f-S) and respectively registered via DRKS Data Management (German Clinical Trials Register, ID: DRKS00012744).

Data will be saved, transferred and retained in accordance with European DSGVO (“Datenschutzgrundverordnung” – General Regulation for Data Protection). The analysis will not allow identification of individual participants, and final reports and publications will only consist of aggregated results.

## Discussion

The aim of the study is to enhance patient reported outcomes after surgical hip or knee replacement by using mHealth with evidence-based content and interface.

It seems reasonable to bring patient education to the next level and adapt it to the needs and conditions of modern society. In recent years, the concepts of eHealth (Electronic Health) and mHealth have become increasingly important in patient-centred health care aiming to enhance patient involvement and self-management capabilities [19, 20]. mHealth intends to capitalize on people’s ubiquitous access to mobile phones to provide 24/7 health care [51]. Ideally, it leads to improved health outcomes by increasing patient knowledge, providing social support, enhancing patient-provider communication and saving resources at the same time [52].

However, there is a lack of evidence for the effectiveness of the use of mHealth in patients undergoing joint replacement [53, 54]. This study will investigate the effects of an evidence-based mobile app as an educational intervention on patient reported outcomes of this target group.

Numbers of joint replacements are increasing and shorter hospital stays require solid self-management skills. Evidence supporting the use of mHealth to potentially improve patient outcomes is of particular importance to open up new possibilities for patient care.

A major limitation of the study is the non-randomized assignment of participants. Therefore the comparability of the groups regarding all relevant patient characteristics will be comprehensively analysed.

A second limitation is a potential mode effect due to different survey modes (online based vs. tablet based) at baseline and 3 months post-surgery.

Another limitation and potential source of bias is the exclusion of participants assigned to the intervention group, but who failed to download or access the app. We have chosen to do this because those participants miss out on engaging with app contents for the preoperative phase that are expected to have an effect on primary and secondary outcomes. We will, however, analyse and report patients’ reasons for not engaging and consider this aspect regarding the generalisability of our findings.

Design and structure of the app were specifically developed to meet the needs of an older target group. However, a lack of patient technology literacy cannot be entirely eliminated, thereby, as a further limitation, negatively affect patient adaptation and compliance to mobile intervention.

### Trial status

At the time of submission of the manuscript in May 2019, recruitment of the patients for the control group is ongoing. App development is in the final testing phase.

## Data Availability

Not applicable.

## Abbreviations

ADL: Activities of daily living
DSGVO: “Datenschutzgrundverordnung” – General Regulation for Data Protection
eHealth: Electronic Health
ERP: Enhanced recovery programmes
HADS: Hospital Anxiety and Depression Scale
HOOS: Hip disability and osteoarthritis outcome score
ICD: International Statistical Classification of Diseases and Related Health Problems
IPAQ: International Physical Activity Questionnaire
KOOS: Knee injury and osteoarthritis outcome score
mHealth: Mobile Health
NRS: Numerical rating scale
OPS: “Operationen- und Prozedurenschlüssel” – key for surgery procedures
THR: Total hip replacement
TKR: Total knee replacement
